## Study aims and hypotheses

The overarching aim of this project is to assess the impact of a multi-model eHealth group behavioral intervention on patient activation among persons living with HIV. The specific aims and hypotheses are shown in Table 1 below.

**Table 1 Tab1:** Study Aims and Hypotheses

Aim 1: Improve PLWH’s empowerment
H 1.1: We will improve patient activation; decision making ability; and perceived knowledge, comfort, and perceived skills at finding, evaluating, and applying electronic health information to health problems.
H 1.2: We will improve clinicians’ communication skills as perceived by PLWH.
Aim 2: Increase PLWH’s receipt of evidence-based care
H 2.1: We will improve patient confidence in adhering to combination antiretroviral treatment (cART), self-reported adherence to cART, and HIV viral suppression (undetectable viral load).
H 2.2: We will increase receipt of evidence-based clinical preventive services.
Aim 3: Improve PLWH’s health
H 3.1: We will improve mental, social, and overall health
Aim 4: Reduce disparities in PLWH’s empowerment
H 4.1: We will produce the greatest improvement in activation for those with lowest baseline activation.
H 4.2: We will observe comparable improvements by race, ethnicity, and education.

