## Methods

### Study design

We will conduct a parallel randomized controlled trial. This design allows us to examine pre- and post-assessments of participants randomized to the intervention (treatment group) compared to participants randomized to usual care (control group). Given our focus on individual patients, the nature of our intervention, including its reliance on training and specific tools, the risk for contamination between participants will be relatively small. Any such contamination will bias results towards the null. We considered other designs including randomizing by practice site (cluster RCT), stepped wedge and staggered enrollment trials, but did not choose these designs due to few clusters, data collection burden, and relatively short funding time frame (3 years).

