#### Clinician training

We will train clinicians to engage patients in the intervention group, (i.e. those who present with their ePHR in the visits) through an educational “lunch and learn” session that is CME-accredited. These educational sessions will address the purpose of the project and basic clinician behaviors to facilitate empowerment. Drs. [name] and [name] will lead these sessions. We will use training approaches used in previous studies [17–19] that are supported by systematic reviews of randomized controlled trials of clinician training [20, 21]. We include explicit demonstrations using brief videos [22]. We will show examples of effective and ineffective communication. These include encouraging the patient to use their ePHR for questions, praising patients for engagement, helping patients prioritize their questions, and providing patients with relevant information to enter into their ePHR. Clinicians will be encouraged to download URHealth onto their own personal devices, in order to familiarize themselves with the ePHR and to enable them to provide ongoing support and effective answers to questions from their patients about use of the ePHR.

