### Study outcomes and measures

Our study measures reflect our patients’ choice of outcomes related to empowerment including activation, eHealth literacy, and greater decision-making and involvement in care. These outcomes will be assessed using validated scales with sound psychometric properties and through chart abstraction data. These are summarized below (Table 4).

**Table 4 Tab4:** Study measures, data source, and timing

Construct (Hypothesis)	Measure	Data type source	Collection points
Participant characteristics			
Demographics	Standardized questions	Survey	T0
Computer experience	Standardized questions	Survey	T0
Health history	Standardized questions	Survey	T0
Aim 1 (Empowerment)			
Patient activation (H1.1)	PAM [56, 57]	Scale	T0, T1, T2
Decision making (H1.1)	Decision Self Efficacy Scale [26]	Scale	T0, T1, T2
eHealth Literacy (H1.1)	eHEALS [23, 24]	Scale	T0, T1, T2
Involvement in Care (H1.2)	Perceived Involvement in Care [25]	Scale	T0, T1, T2
Aim 2 (Evidence-based care)			
HIV adherence self-efficacy (H2.1)	ASES [29]	Survey	T0, T1, T2
Adherence to cART (H2.1)	Past week adherence [28]	Survey	T0, T1, T2
HIV viral load <50 (H2.2)	HIV viral loads (both actual level; and whether undetectable or not)	Chart abstraction	T0, T2
Evidenced based preventive care	Cancer screening/immunizations [58]	Chart abstraction	T0, T3
Aim 3 (Health)			
Physical and Mental health/Quality of Life (H3.1)	SF-12 [27]	Scale	T0, T1, T2
Aim 4 (Moderators)			
Low Activation (H4.1)	PAM and eHEALS (<median)	Scales	T0
Minority race/ethnicity (H4.2)	Standardized questions	Survey	T0
Low education (4.2)	Standardized questions	Survey	T0
Clinician patient centeredness	Instrument on Doctor-Patient Communication Skills. [30]	Scale	

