#### Patient empowerment

Our primary outcome is patient empowerment assessed using the Patient Activation Measure (PAM). We will capture related additional dimensions of empowerment including eHealth literacy (eHealth Literacy Scale eHEALS [23, 24]), patient involvement in their care (Patient Involvement in Care [25]) and, patient confidence in their health care decision making (Decision Making Self Efficacy Scale [26]).

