#### Clinician communication

We will assess the communication skills of clinicians using the Doctor-Patient Communication Skills instrument [30]. This validated scale assesses key aspects of clinician communication from the perspective of the patient. We will minimize patient reporting bias by aggregating clinician scores across patients. We chose to use patient ratings of clinicians rather than observer ratings because these are more patient-centered measures and patients’ perceptions probably have the greatest impact on patients’ behavior; as well as their lower costs and greater capacity for pragmatic implementation. We chose this scale over other patient reported measures of clinician communication because it comes closest to measuring the clinician competencies that we address in our clinician training and which our patients tell us are most meaningful to them.

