### Aim 1: Improve PLWH’s empowerment

To assess H 1.1 (Improvement in patient activation; decision making ability; and perceived knowledge, comfort, and perceived skills at finding, evaluating, and applying electronic health information to health problems), we will compare changes in patient activation (primary outcome), eHealth literacy, and decisional self-efficacy outcomes by assigned randomization group using GEE models that control for baseline scores. All models will be adjusted for any potential confounders identified by the initial analyses. We will use the same approach to assess H 1.2 (substituting Perceived Involvement in Care).

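### H1.2 is about clinicians' communication skills, but its only planned test uses a measure of patient involvement, so a positive result would not show better clinician communication

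*Protocol article*

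**What the plan says.** **The hypothesis.** Table 1 (Study aims and hypotheses) states H1.2 as "We will improve clinicians’ communication skills as perceived by PLWH".

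**The test.** The Aim 1 analysis section gives one analysis: "We will use the same approach to assess H 1.2 (substituting Perceived Involvement in Care". Table 4 agrees. Its row "Involvement in Care (H1.2") lists the Perceived Involvement in Care scale at T0, T1 and T2. The Patient empowerment section places this scale among the additional dimensions of empowerment, as "patient involvement in their care (Patient Involvement in Care [25").

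**The communication instrument.** The Clinician communication section says "We will assess the communication skills of clinicians using the Doctor-Patient Communication Skills instrument [30"]. It prefers this scale because it is the nearest match to the skills in the clinician training. On scoring it says "We will minimize patient reporting bias by aggregating clinician scores across patients". Table 4 lists the instrument under Aim 4 (Moderators), labelled as clinician patient-centeredness, with no hypothesis number. None of the four Aim analysis sections uses it as an outcome.

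**The clinician component.** Clinician education is the fourth of four intervention components (Abstract). The Clinician training section says "We will train clinicians to engage patients in the intervention group", and goes on to define these as patients who bring their ePHR to the visit. Controls receive usual care from their own HIV clinician (Usual care). Individual patients are randomised, stratified by Rochester or NYC. The Study design section judges that "the risk for contamination between participants will be relatively small" and that any contamination would bias toward the null.

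**The concern.** A hypothesis about what clinicians do is tested with a score for how involved patients feel. The patient-level components act on involvement directly: group sessions teach participants to form, rank and ask questions with role play, and the pre-visit coaching rehearses them. A gain in perceived involvement could come entirely from the patient's side of the visit. Read under H1.2 as worded, it would count as evidence that clinicians communicate better.

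The related issue is where the effect of clinician training goes. If a trained clinician sees patients from both arms, any general change in that clinician's manner reaches controls too and drops out of the arm contrast. The contamination statement covers transfer between participants only. A hypothesis about clinician skill is the one most exposed to this.

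**Working it through.** **1. Hypothesis against test**

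| Section | Construct | Measure | Role |
|---|---|---|---|
| Table 1, H1.2 | Clinicians' communication skills, as perceived by patients | none named | Hypothesis |
| Aim 1 analysis; Table 4 | Involvement in care | Perceived Involvement in Care | Outcome for H1.2 |
| Patient empowerment | A dimension of patient empowerment | same scale | Additional outcome |
| Clinician communication | Clinicians' communication skills | Doctor-Patient Communication Skills | No hypothesis named |
| Table 4, Aim 4 | Clinician patient-centeredness | same instrument | Moderator |

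The construct in H1.2 matches the instrument that is not tested, and the instrument that is tested is assigned elsewhere to a different construct. The collection-point cell for the communication instrument appears empty, but table extraction may explain that, so nothing here rests on it.

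**2. The protocol's detectable effect**

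Inputs from the Power section: 360 enrolled, 15% drop-out, 8 sites, ICC 0.0207, 80% power; two-sided 5% from Planned analysis. Equal allocation is assumed.

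- Evaluable: 360 × 0.85 = 306, or 153 per arm; 306/8 = 38.25 per site.
- Design effect: 1 + 37.25 × 0.0207 = 1.771.
- d = (t0.975,6 + t0.80,6) × √(2 × 1.771/153) = 0.510.

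The stated 0.51 is reproduced. It is claimed for the measures in Table 6, which include Perceived Involvement in Care but not the communication instrument.

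**3. If the clinician-aggregated score were used as an outcome**

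Suppose each patient is given the mean score of their clinician, pooled over both arms, with K clinicians, N = 306 and patients randomised regardless of clinician. On average a share (K − 1)/(N − 1) of the true arm difference survives.

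- K = 8: 0.51 × 7/305 = 0.012 SD (simulation 0.011).
- K = 40: 0.51 × 39/305 = 0.065 SD (simulation 0.066).

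About 87% to 98% of the difference is lost. K is assumed, as the protocol gives no number of clinicians. Aggregating separately by arm would keep a contrast.

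**4. Spillover through clinicians**

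Suppose controls receive a share f of a 0.51 SD effect. The contrast becomes 0.51 × (1 − f).

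| f (assumed) | Contrast, SD | Power, cluster formula of step 2 | Power, 153 per arm, no design effect |
|---|---|---|---|
| 0 | 0.51 | 80% | 99% |
| 0.10 | 0.459 | 71% | 98% |
| 0.25 | 0.383 | 56% | 92% |
| 0.50 | 0.255 | 29% | 61% |

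Both power columns are shown because the protocol sizes the trial with a cluster formula but randomises individuals. How likely is sharing? With 1:1 allocation, a clinician with four participants has all four in one arm with probability 2 × (1/2)^4 = 12.5%.

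**The case against.** The strongest reply is that the protocol never names the communication instrument as the H1.2 outcome. Table 4 and the Aim 1 analysis agree that H1.2 is tested with Perceived Involvement in Care, and aggregating ratings by clinician is sensible for a clinician-level moderator, which needs no arm contrast. This stands. Step 3 describes what would go wrong if the score were moved to H1.2 unchanged, not an analysis the protocol plans. It does not remove the mismatch between the wording of H1.2 and its test.

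It can also be said that the involvement scale may contain items on clinician behaviour. The protocol does not give its content and presents it as patient involvement. If such items exist, the gap is narrower.

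A reader might go further and infer that H1.2 and the four-component package cannot be answered at all, that the expected arm difference is zero, or that controls are fully exposed to clinician training. The documents do not support this:

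- Pooling across arms is not stated.
- Shared clinicians are a strong inference from individual randomisation; caseloads, training uptake and timing are not given.
- Seeing a trained clinician is not the same as receiving the trained behaviour. Much of the training concerns responding to the ePHR, which controls do not receive until after T3. That part stays in the contrast, so conclusions need not be confined to the patient-level components.
- Spillover biases toward the null, the direction the protocol already gives for contamination.

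The Discussion concedes that the effects of separate elements cannot be disentangled. That differs from saying controls may receive part of one of them.

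**Conclusion.** The mismatch is explicit and rests on no outside assumption: H1.2 claims a change in clinicians, and its only test measures patients' involvement. A positive result would support a statement about involvement only. The instrument that fits the wording has no outcome analysis and no stated detectable effect.

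The contamination point is smaller and conditional. It rests on trained clinicians treating both arms and on some of the training effect being general. Its size depends on a share that the protocol does not give; the figures in step 4 are illustrations.

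This concerns a secondary hypothesis and the description of the comparison. The intention-to-treat comparison of patient activation remains valid, at most diluted.

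**What to change.** Reconcile Table 1, Table 4, the Clinician communication section and the Aim 1 analysis in one of two ways.

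- **(a) Match the outcome to the hypothesis.** Make individual patients' communication-skills ratings the H1.2 outcome, collected at baseline and T2 in both arms and compared by arm in the planned baseline-adjusted GEE. Keep the clinician-aggregated score only as a moderator. Report Perceived Involvement in Care as a separate outcome.
- **(b) Match the hypothesis to the outcome.** Reword H1.2 to perceived involvement in care and limit its conclusion to that.

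Under either option, extend the contamination statement in Study design. It should say that with individual randomisation trained clinicians may also treat usual-care patients, that any general training effect shared by both arms is diluted out of the contrast (bias toward the null), and that clinician behaviour triggered by the ePHR remains arm-specific.

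Option (b) and the contamination sentence cost only wording. Option (a) adds at most one scale to two existing surveys. The randomisation, sample size and primary analysis do not change.

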### Aim 2: Increase PLWH’s receipt of evidence-based care

To assess H 2.1 (improvement in patient improve patient confidence in adhering to combination antiretroviral treatment (cART), self-reported adherence to cART, and HIV viral suppression), we will substitute these dependent variables in the above models. Similarly for H 2.2 (improvement in evidence-based care), we will index for evidence-based care for the dependent variable. This index will be created by passed on ratio of interventions that the patient received versus the number they were eligible for.

### Aim 3: Improve PLWH’s health

To assess H 3.1 (improvement in mental, social and overall health) we will use the same approach substituting the scores from the SF-12 physical and mental health components.

### Aim 4: Reduce disparities in PLWH’s empowerment

To assess H 4.1 (greatest improvement in patient activation will be seen in those with lowest baseline activation scores), we will enter interaction terms into the models with treatment assignment. The interaction terms will be based on median cut-offs for activation. To assess H 4.2. (comparable improvements in by race, ethnicity and education). We repeat the above process using an interaction term between treatment assignment and the sociodemographic characteristics.

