#### Patient social disadvantages

We will assess race (White, Black, Asian, Other) and ethnicity (Latino or not), age, and sex based on self-report. We define low education as absence of any high school degree. Low activation and low eHealth literacy will be based on less than the median value on the PAM and eHEALS.

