### Planned analysis

Following collection and cleaning of data (T0–T3), the underlying assumptions of all analyses will be checked using appropriate graphical and numerical methods [31]. Data accuracy will be investigated upon discovery of any outliers or influential data points. If an outlier is detected, we will truncate the outlier by assigning a reasonable value or replacing it using the adjacent values from the remaining data. We will try to utilize all data points in the final analysis.

The proposed study adopts a randomized repeated measures pre-test/post-test design and our analytic plan reflects this design. We will use generalized estimating equations (GEE) to obtain robust estimates and to account for the repeated measures study design and the correlated data structure of subjects nested within study site [32]. The chosen link function for the models will be appropriate for the distribution of each outcome. Unless otherwise stated, all statistical tests will be performed at the two-tailed 5 % level of significance. Likewise, 95 % confidence intervals will be constructed for estimation of effects (e.g., difference in outcomes between intervention and control groups). We will use Dunnett and Hsu’s methods to control for multiple comparisons in secondary outcomes [33]. All analyses will be performed with SAS® statistical software version 9.3 (SAS Institute, Cary NC).

We will summarize frequencies of categorical variables and means or medians for continuous and ordinal variables. Continuous variables with skewed distributions will be transformed to approximate normality. We will construct tables that display baseline characteristics for participants, overall and by (blinded) group assignment. We will compare baseline information on participants including demographic characteristics, previous computer use, and health factors. We will assess whether attrition differs across baseline characteristics or by group assignment and adjust for differences if present using multiple imputation if necessary. We will conduct intention-to-treat analyses.

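### H 4.1 predicts a gradient in benefit across baseline activation but is tested on a median split; a continuous interaction fits the hypothesis better and, if the gradient is roughly linear, has more power

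*Protocol article*

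**What the plan says.** Table 1 of the protocol article words H 4.1 as a statement about the bottom of the scale: "We will produce the greatest improvement in activation for those with lowest baseline activation".

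The analysis is fixed in the section on Aim 4: "we will enter interaction terms into the models with treatment assignment", followed by "The interaction terms will be based on median cut-offs for activation". The section on patient social disadvantages defines the groups: "Low activation and low eHealth literacy will be based on less than the median value on the PAM and eHEALS". Table 4 repeats the rule in its H 4.1 row, where the measure is "PAM and eHEALS (<median". The cut is therefore stated in three places and is not a detail left open for a separate analysis plan.

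Table 4 also shows that PAM is collected as a scale at T0. The Aim 1 section, whose models carry over to Aim 4, specifies "GEE models that control for baseline scores". The article gives no reason for the cut and mentions no interaction with the score itself. The Power section reports Monte Carlo simulations giving at least 80% power for the H 4.1 and H 4.2 interactions, without the inputs.

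**The concern.** Hypothesis and test do not match. A contrast of two halves treats a participant just below the median as equal to the least activated participant, and as opposite to someone one point higher. A significant result would say that the halves differ; it would not locate the greatest benefit at the lowest scores.

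The cut has two further costs. No external threshold is given, so the natural reading is the median of whoever enrols. The pilot was also split at its own group median, so low activation need not mean the same thing in the pilot and in the trial. And if benefit changes steadily with baseline PAM, splitting the score discards information about the interaction, which is usually among the least powerful tests in a trial. H 4.1 carries the claim that the least activated patients gain most.

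**Working it through.** **Inputs.** From the Power section: 360 enrolled, 15% drop-out, 8 sites, ICC 0.0207, 80% power. From Planned analysis: "all statistical tests will be performed at the two-tailed 5 % level of significance". From Table 6, patient activation row: 0.52 (low activation) and −0.155 (high activation). Assumed: 1:1 allocation, effects in units of the residual SD, the same residual SD for both tests.

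**1. The plan's own figures.** Completers: 360 × 0.85 = 306, or 153 per arm. The design effect is 1 + (306/8 − 1) × 0.0207 = 1.771. With t quantiles on 8 − 2 = 6 degrees of freedom, (2.447 + 0.906) × √(2 × 1.771/153) = 0.51. This reproduces the stated detectable effect for H 1.1 to H 3.1 and supports using 306 and equal arms. The 80% for the interactions cannot be reproduced strictly because its inputs are not given; step 2 checks whether it is plausible.

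**2. Power of the planned split.** Four equal cells of 306/4 give an SE for the interaction of √(16/306) = 0.2287. The contrast detectable with 80% power is (1.96 + 0.84) × 0.2287 = 0.64. The pilot contrast is 0.52 − (−0.155) = 0.675, so z = 0.675/0.2287 = 2.95 and power is Φ(2.95 − 1.96) = 84%. This agrees with the stated minimum of 80%.

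**3. What the split keeps if the gradient is linear.** Let the effect change by b per SD of a normal baseline score, with residual SD σ.
- Continuous interaction: SE = 2σ/√N, so z = 0.5 b√N/σ.
- Median split: the halves differ by 2√(2/π) = 1.596 SD, so the contrast is 1.596b with SE 4σ/√N, and z = 0.399 b√N/σ.
- Ratio 0.399/0.5 = 0.798; squared, 2/π = 0.637. The loss is 36%, and 306 completers act like about 195.

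A variance inflation common to both tests, such as one for site, cancels from this ratio.

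**4. Dependence on the shape of the baseline score.** The information lost is one minus the squared correlation between the score and the below-median indicator.

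| Shape | Loss |
|---|---|
| Uniform | 25% |
| Bimodal | 25% |
| Normal with ceiling at +1 SD | 32% |
| Normal | 36% |
| Gamma (shape 4) | 41% |
| t, 5 df | 46% |
| Lognormal (σ 0.5) | 48% |
| Laplace | 50% |

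The article gives no PAM distribution. Planned analysis says "Continuous variables with skewed distributions will be transformed to approximate normality", which makes the normal case a reasonable centre but does not establish it.

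**5. Power of the two tests (normal score, linear gradient).** The continuous z is the split z divided by 0.798.
- Contrast 0.675: split 84%; continuous Φ(2.95/0.798 − 1.96) = 96%.
- Contrast 0.5 (illustrative): z = 0.5/0.2287 = 2.19; split Φ(0.23) = 59%; continuous Φ(2.19/0.798 − 1.96) = 78%.

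**6. Simulation** (4,000 runs, N = 306, continuous baseline in both models). At 0.675 with a linear gradient, power was 82% for the split and 95.5% for the continuous test. With a true step of 0.675 at the median, the order reverses: 84% and 65%. With no interaction, the rejection rates were 4.8% and 5.1%.

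**The case against.** The cut is pre-specified, so there is no search for a favourable threshold, and type I error is sound. Aim 4 is framed around disparities between groups: low activation is defined beside low education, race and ethnicity, and the pilot results use the same rule. A two-group contrast is easy to read and assumes no shape. A straight-line interaction does assume one, and does not by itself prove that benefit peaks at the lowest scores. All of this stands. It is why the split should remain as a display and why the continuous test needs a non-linearity check.

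Two readings of the text are natural but not stated word for word: that the median is that of the enrolled sample, and that the baseline score enters the model as a continuous covariate.

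A reader might infer that H 4.1 is underpowered, or that the 80% in the Power section is wrong. The documents do not support either: the split reaches about 84% at the pilot contrast. A reader might also take the 36% as a fixed property of the plan. It is not in the documents and holds only for a near-normal score with linear modification.

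It could be said that eHEALS is out of scope because the Aim 4 section names activation alone. This does not stand, because Table 4 lists eHEALS in the H 4.1 row.

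**Conclusion.** The point holds as a cheap improvement, not as a failed test. The mismatch between a gradient hypothesis and a test of two halves follows from the text and needs no assumption.

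The loss of power is conditional. With roughly linear effect modification it is an assumed 25% to 50% of the information on the interaction. At a contrast of 0.675 that means about 84% against 96%, with 306 completers, 1:1 allocation and a normal score. The loss concerns the H 4.1 interaction only; the primary comparison is untouched.

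It matters more if the pilot was optimistic. The 0.675 comes from pre-post changes in 32 participants, with no control group described, split on the baseline of the same score, so regression to the mean may have inflated it.

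**What to change.** Replace the sentence on median cut-offs in the Aim 4 section with wording such as: H 4.1 is tested by the interaction between treatment assignment and continuous baseline PAM; linearity is checked with a pre-specified spline; predicted treatment effects with confidence intervals are shown at low, middle and high baseline PAM; results by median split are given descriptively, for comparison with the pilot. Do the same for baseline eHEALS, which Table 4 lists as an H 4.1 moderator, and align the Aim 4 section with that table. Bring the definition of low activation under patient social disadvantages into line by marking it as descriptive.

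The cost is a few sentences and no new data. The price is the assumed shape: if the effect truly steps at the median, the linear test has about 65% power against 84% for the split. Nothing in the article points to such a step, and the spline check is there to reveal marked non-linearity.

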**Discussion:**

We hypothesize that participants receiving the intervention will show greater improvement in empowerment and the intervention will reduce disparities in study outcomes. Disparities in these measures will be smaller than those in the usual care group. Findings have implications for activating persons living with HIV and for other marginalized groups living with chronic illness.

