### Power

The number of participants included in the intervention group and the usual care groups is based upon a series of power analyses. For H 1.1 – H 3.1, we estimated detectable difference using the method described by Donner and Klar, [36] using 8 study sites total, a significance level of 0.05, and a minimum power of 80 %. The intra-cluster correlation (ICC = 0.0207) was estimated from our pilot data and is consistent with other studies [37]. We plan to enroll 360 participants to allow for attrition and assume a 15 % drop-out rate. Thus, we will be able to detect an effect size of 0.51 for each of the measures in Table 6. For H 4.1 and H 4.2, we ran Monte Carlo simulations to determine that we will have a minimum of 80 % power for the interactions [38].

**Table 6 Tab6:** Change in empowerment dimensions (effect size) by participant education, activation or eHealth literacy

Empowerment dimension	<High school	High school	>High school	Low activation	High activation	Low eHealth literacy	High eHealth literacy
HIV adherence self-efficacy	0.15	−0.64	−0.19	0.18	−0.38	−0.02	−0.05
eHealth literacy	0.85	0.35	0.61	0.98	0.18	0.94	0.35
Perceived Involvement in Care	0.57	0.37	0.24	0.61	0.11	0.48	0.26
Decision self-efficacy	0.81	0.23	0.34	0.86	0.16	0.48	0.52
Patient Activation	0.50	−0.85	0.24	0.52	−0.155	0.32	0.11

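### H4.2 predicts comparable benefit by race, ethnicity and education, but its only planned analysis is a test for difference, and equal gains would not shrink those disparities

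*Protocol article*

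**What the plan says.** Table 1 (Study aims and hypotheses) places two hypotheses under the aim of reducing disparities. H4.1 expects the largest gain in activation among those with the lowest baseline activation. The other reads: "H 4.2: We will observe comparable improvements by race, ethnicity, and education".

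The Aim 4 analysis section tests H4.1 by a treatment interaction: "The interaction terms will be based on median cut-offs for activation". For H4.2 it then says: "We repeat the above process using an interaction term between treatment assignment and the sociodemographic characteristics". Under Planned analysis, unless otherwise stated, "all statistical tests will be performed at the two-tailed 5 % level of significance". Planned analysis also promises 95% confidence intervals for effects. No criterion is given for what would count as comparable.

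The Power section treats the two hypotheses alike: "we ran Monte Carlo simulations to determine that we will have a minimum of 80 % power for the interactions". The abstract's Discussion forecasts that the intervention will reduce disparities in outcomes and adds: "Disparities in these measures will be smaller than those in the usual care group".

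**The concern.** H4.1 predicts a difference between subgroups and H4.2 predicts none, yet both get the same test and the same power statement. For H4.2 the prediction coincides with the null hypothesis. A significant interaction would count against it. A non-significant one says only that a difference was not detected, which a modest subgroup sample makes likely whether or not a difference exists. The design therefore has no outcome that supports H4.2.

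The hypothesis also pulls against its own aim. If every group gains equally, the gaps between groups stay where they were.

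Aim 4 is the trial's equity question. At stake is whether a group that gains clearly less could end up described as benefiting equally, and whether a finding of equal benefit could be presented as a reduction in disparity. A smaller matter is that H4.1 is tested on a dichotomised score, which costs power for no evident gain.

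**Working it through.** **The plan's own figure first.** Inputs from the Power section: 360 enrolled, 15% drop-out, 8 sites, ICC 0.0207.
- Completers: 360 × 0.85 = 306, or 153 per arm if 1:1 (ratio not stated; assumed).
- Mean per site: 306/8 = 38.25. Design effect: 1 + 37.25 × 0.0207 = 1.771.
- Detectable main effect: (t₀.₉₇₅,₆ + t₀.₈₀,₆) × √(2 × 1.771/153) = (2.447 + 0.906) × 0.1522 = 0.51.

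This reproduces the stated 0.51, which applies to H1.1–H3.1. The 80% for the interactions cannot be reproduced, because the simulated effect is not given.

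**How often a real deficit would be missed.** Further inputs: low-education share p = 0.31 (10 of 32 in pilot Table 5, assumed to carry over to the trial); two-sided 5%; an illustrative true deficit of 0.3 SD; no design effect, since randomisation is individual and stratified by region.

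SE of the interaction in SD units = k × √(4/(N p(1−p))), where √(4/(306 × 0.31 × 0.69)) = 0.247 and k is the residual SD after adjustment.
- Unadjusted: k = 1.
- Baseline-adjusted, assumed r = 0.6: k = √(1 − 0.36) = 0.8.
- T1 and T2 averaged, baseline-adjusted, assumed T1–T2 correlation ρ: k = √((1 + ρ)/2 − 0.36), which is 0.663 at ρ = 0.6 and 0.735 at ρ = 0.8.

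P(non-significant) ≈ Φ(1.96 − 0.3/SE), ignoring the negligible opposite tail.

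| Model | SE | P(non-significant) if true deficit is 0.3 SD | 95% CI half-width |
|---|---|---|---|
| Unadjusted | 0.247 | 77% | 0.48 SD |
| Baseline-adjusted | 0.198 | 67% | 0.39 SD |
| T1/T2 averaged, ρ = 0.6 | 0.164 | 55% | 0.32 SD |
| T1/T2 averaged, ρ = 0.8 | 0.182 | 62% | 0.36 SD |

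The protocol controls for baseline scores (Aim 1 analysis section), so the adjusted rows are the relevant ones. The half-widths also show that an interval could never fall wholly inside a margin narrower than about 0.3–0.4 SD, even with an estimate of exactly zero.

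**Equal gains and the gap.** Let groups A and B have usual-care means a and b. If both gain Δ, the intervention-arm gap is (a + Δ) − (b + Δ) = a − b, the same as under usual care. A smaller gap requires the lower group to gain more. H4.1 predicts that, but only by baseline activation; H4.2 predicts the opposite for race, ethnicity and education. The Preliminary data section also reports that the least educated benefited most in the pilot, which fits a reduction better than it fits H4.2.

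**Median split for H4.1.** Assume linear moderation of 0.25 SD per SD of baseline PAM, r = 0.6, N = 306.
- Continuous: SE = 0.8 × 2/√306 = 0.0915; 0.25/0.0915 = 2.73; power about 78% (simulated 77%).
- Median split: contrast = 0.25 × 2√(2/π) = 0.399; SE = 0.8 × √(4/(306 × 0.25)) = 0.183; ratio 2.18; power about 59% (simulated 57%, because moderation left within each half adds noise).

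**The case against.** - **The protocol never says that p > 0.05 will count as proof of H4.2.** True. A reader might infer that non-significance would be reported as equal benefit, but the text does not state that rule. It also promises 95% confidence intervals, and an unseen analysis plan could hold a margin. What stands is narrower: the test the protocol names cannot support the hypothesis it is assigned to, and the power statement treats detecting a difference and showing similarity as one thing. That is a mismatch in the text, not an omission.
- **A reader might infer that the 80% interaction power is not achieved.** The document does not support this. It names no simulated effect, and the 0.51 belongs to the main effects. At the pilot's low-versus-high activation contrast in Table 6 (0.52 − (−0.155) = 0.675), power for a median split is 84% unadjusted and 96% with baseline adjustment at r = 0.6.
- **A reader might also dismiss that pilot contrast as regression to the mean.** The pilot change is uncontrolled, but the extent cannot be determined from the document, and the trial's randomised interaction test is protected by its control arm.
- **Reducing disparities is coherent for baseline activation.** Agreed. The protocol lists low activation among its social disadvantages, and H4.1 predicts larger gains there. The conflict is confined to race, ethnicity and education.
- **The median split is prespecified and consistent.** It is, and the gain from a continuous term depends on the assumed linear moderation. It is a cheap improvement rather than an error.

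**Conclusion.** The concern holds for H4.2. A similarity hypothesis has been given a difference test, and the claimed power does not bear on it. Under the planned baseline-adjusted analysis, a 0.3 SD shortfall in low-education patients would be non-significant about 55–67% of the time. This range assumes 1:1 allocation, the pilot's 31% share, baseline r = 0.6, T1–T2 correlation of 0.6–0.8 where the two are averaged, and no design effect. The conflict between H4.2 and the abstract's claim of smaller disparities also holds, on the scale of differences in means, and needs no numerical assumption. The median split is secondary.

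The randomised primary comparison is unaffected, and Aim 4 is a moderator aim, so this should be fixed but does not threaten the trial's main conclusion.

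**What to change.** 1. In the Aim 4 analysis section, state that a non-significant interaction does not support H4.2. Report each treatment-by-characteristic interaction with its 95% confidence interval. Claim comparability only if the interval lies within a prespecified margin; otherwise report the result as inconclusive.
2. Reconcile H4.2 with the Aim 4 title and the abstract: either hypothesise larger gains in the disadvantaged groups, or limit the disparity-reduction claim to baseline activation.
3. Test H4.1 with the interaction of treatment and continuous baseline PAM, and keep the median split for display.

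The cost is wording; no data collection or sample size changes. The small downside is that H4.2 will probably end as an estimate with a wide interval, since half-widths of roughly 0.3–0.4 SD leave little room to meet a tight margin.
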